### Study Setting

The study population consists of patients and clinicians at two federally qualified community health centers in inner-city Rochester, NY. The health centers provide a full range of primary care services to a predominantly low-income and/or uninsured, ethnically and culturally diverse patient population including African, African-American, Asian, Asian-American, Eastern European, Hispanic, and several other foreign-born immigrant and refugee patients. There are 15 family physicians, two nurse practitioners, and two physician assistants at the two health centers. In the US, both nurse practitioners and physician assistants have graduate-level education and are licensed and certified to treat a variety of physical and mental health conditions and provide health behavior counseling.

### Participant eligibility

Patient and clinician eligibility criteria are shown in Table 2. Patient eligibility is determined by the Research Assistant reviewing clinicians’ schedules with a checklist of inclusion and exclusion criteria. If eligibility is uncertain, the Research Assistant checks with office staff. Patients are excluded if they are deemed inappropriate for participation due to an acute or unstable medical condition or if they are unable to provide informed consent due to a language barrier, limited literacy, and/or cognitive concerns.

**Table 2 T2:** Inclusion and exclusion criteria

	**Inclusion criteria**	**Exclusion criteria**
Patients	**·** Currently enrolled patients at Westside Health Services, Inc.)	**·** Have a life-threatening or acute medical problem which precludes participation
	**·** Scheduled for a routine, follow-up, or health maintenance office visit	**·** Unable to read and understand English
	**·** Scheduled to see a participating clinician	
	**·** 18 years of age or older	
	**·** Able to provide written informed consent	
	**·** Have one or more stable medical conditions for which activity is not contraindicated (e.g., asthma, patients undergoing chemotherapy, diabetes, hypertension, stable cardiovascular, neurological, or psychiatric disease)	
Clinicians	**·** Practicing clinicians (physicians, physician assistants, or nurse practitioners) at community health center organization	**·** Planning to move or relocate to another practice in the study period
		**·** Serving as study investigators or advisors

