### Procedure for randomization

A concealed randomization procedure stratified by health center location and clinician type (physician, nurse practitioner, or physician assistant) is used to balance randomization between both groups. A series of treatment assignments in a block of five is generated by the study statistician in advance of the intervention and placed in a file accessible to the Research Assistant responsible for administering the group assignment to each clinician. Clinicians are notified of their randomization assignment by the Research Assistant immediately after providing informed consent by opening a sealed envelope with the assigned intervention category for each individual: Group 1 (Early) or Group 2 (Wait-list). Neither study clinicians nor research staff are blind to the assignment of clinicians to the early or wait-list training groups.

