### Patient participant recruitment and enrollment

When potentially eligible patients enter exam rooms for their visit, a nursing assistant mentions the project to see if they might be interested in participating. The Research Assistant then obtains written consent from eligible and interested patients. As part of the informed consent process, patients are told that they are not obliged to deliberately discuss physical activity. The visit is then audio-recorded. As with the clinician informed consent procedure, patients are explicitly informed that if they agree to participate, the recorder is placed unobtrusively in the exam room. The consent process takes about five minutes and is designed for minimal disruption of office flow and schedules. Patients are recruited until there is adequate baseline information about physical activity discussions.

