#### Exploratory outcome measures

Moderation variables consist of patient factors and visit factors. Patient factors are socio-demographic variables, body mass index, baseline health, [58,59] health literacy[60], co-morbidities, and length of relationship with their clinician. Visit factors consist of type of visit, measured categorically using the clinic schedules (e.g. routine follow-up, health care maintenance) and competing demands measured by the 1) number of topics discussed and 1) number of health behaviors discussed.

Mediation variables consist of patient perceived competence for physical activity (using the PCS), clinician autonomy support (using the mHCCQ) for physical activity, and patient recall of 5A using the Physical Activity Exit Interview (PAEI) [47]. The PAEI is a 12-item survey administered to patients after their visit asking them to recall specific content (Yes/No) to questions corresponding to each A for physical activity, such as “Did your doctor advise you to become more physically active?”, “Did your doctor discuss difficult situations you might encounter or problems you might have in trying to become more physically active?”, and “Did your doctor state that he/she is planning to discuss your physical activity on a future visit?”

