**Figure 2 F2:**
[figure not shown]
Mediators and moderators to be assessed in exploratory analyses.

The clinicians will be included as a random effect, and intervention group, time, and baseline 5A scores will be included as fixed effects. The interaction between treatment and time will be used to assess whether the treatment effect (of the intervention) changes with time.

Secondary analyses include similar modeling approaches for the secondary outcome variables: autonomy support (mHCCQ), patient perceived competence (PCS) and clinician feasibility (PAL). Clinician feasibility will also be qualitatively analyzed using the process evaluation data and individual clinician exit interviews. The secondary hypotheses (H2-H4) are as follows:

H 2: The intervention will increase clinician use of the PCC construct autonomy supportiveness as assessed by the mHCCQ in the post-intervention period (immediately post and at one year) compared to baseline.

H 3: The intervention will increase patient perceived competence (accessed via the PCS) for adopting physical activity.

H 4: Specific patient recall of the Assist and Arrange will be associated with the greatest patient perceived competence to adopt physical activity compared to recall of Ask, Advise, or Assess.

Hypotheses 2–4 will be tested by measuring the changes in the mHCCQ, PCS, and PAEI scores, respectively, for patients seen by clinicians in Group 1 in the post-intervention period (immediately post and at one year) compared to baseline. compared to the Group 2 baseline and Group 1 baseline. We will also compare change in the 5A scores for Group 2 post-intervention compared to Groups 1 and 2 baseline scores.

Exploratory analyses will use a similar approach to that used for the primary analysis, to examine whether the primary outcome (5A score) was mediated by patient perceived competence (PCS score), clinician autonomy supportiveness (mHCCQ score), or patient recall of the 5As (PAEI score). Additional exploratory analyses will examine the role of selected factors that may moderate the relationship between the intervention and the 5A score: continuity of care, patient socio-demographic variables, patient BMI, baseline health, health behaviors, health literacy, and competing demands. Regression-based statistical models will be constructed and examined. The Diagram below shows the inter-relationship of the mediating and moderating factors to be explored in this analysis.

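### Visit type is collected and listed as a moderator but is left out of the primary 5As model, so a change in visit mix could bias the post-versus-baseline comparison

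*Protocol article*

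**What the plan says.** All references are to the protocol article.

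- **Which visits count.** Table 2 (Participant eligibility) admits patients who are "Scheduled for a routine, follow-up, or health maintenance office visit".
- **Who screens and approaches.** Under Participant eligibility, "Patient eligibility is determined by the Research Assistant reviewing clinicians’ schedules with a checklist of inclusion and exclusion criteria". Under Patient participant recruitment and enrollment, "a nursing assistant mentions the project to see if they might be interested in participating", after which the Research Assistant takes consent.
- **Blinding at recruitment.** Procedure for randomization: "Neither study clinicians nor research staff are blind to the assignment of clinicians to the early or wait-list training groups". The coders of the recordings are blinded to clinician and time point (Primary outcome measure).
- **Who is compared.** Hypothesis H1 sets visits after training against baseline visits. Design limitations and other considerations concedes that the same patients are not followed across time points.
- **Visit type is measured.** Exploratory outcome measures, among the moderation variables: "Visit factors consist of type of visit, measured categorically using the clinic schedules (e.g. routine follow-up, health care maintenance".
- **Visit type is not in the model.** Statistical analyses: clinician is a random effect, and "intervention group, time, and baseline 5A scores will be included as fixed effects". The moderators listed in that section include competing demands but not visit type.

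**The concern.** A health maintenance visit and a follow-up visit for a chronic condition may offer different room for talk about physical activity. The plan accepts that visit type may matter, since it records the variable and names it as a moderator.

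Each time point draws new patients, about 10 per clinician at baseline and seven or eight at each later point. The share of each visit type can therefore change between time points. If types differ in mean 5As score, such a change moves the group mean even when clinicians counsel any given kind of visit exactly as before. The stated model has no term to take this out. The baseline score term does not do so: with different patients at each point it can only summarize the clinician's baseline visits, and says nothing about the mix of the later ones.

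At stake is the reading of H1, which is worded as a change from baseline.

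**Working it through.** **1. Yardstick.** Sample size and power gives a planned difference of 0.54 between groups, SD 1.06, with 15 clinicians (8 and 7) and 20 visits each. Treating visits as independent:

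(1.960 + 0.842) × 1.06 × √(1/160 + 1/140) = 0.3437

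So 0.54 is not reproduced from those inputs alone. It would need a design effect of (0.54/0.3437)² = 2.47, that is, an intraclass correlation of (2.47 − 1)/19 = 0.077. The article says clustering was considered but states no value. I use 0.54 only as a sense of scale, and the point does not depend on it.

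**2. How a change in mix enters the estimate.** Simplify to two visit types with a gap *g* in mean score, and let *Δ* be the change in share of the higher-scoring type from baseline to post.

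- Bias in the within-group contrast = *g* × *Δ*
- Bias in the between-group contrast = *g* × (*Δ*₁ − *Δ*₂), for Groups 1 and 2

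If both groups shift by 20 points and *g* = 1.0, each within-group change is off by 0.20 and the between-group comparison by 0. If Group 1 shifts by 20 points and Group 2 by 10, the between-group comparison is off by 1.0 × 0.10 = 0.10, or 0.10/0.54 = 19% of the yardstick.

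**3. Range under assumptions.** The documents give no visit mix and no score by type. Every *g* and *Δ* below is assumed.

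| Gap *g* | *Δ* = 0.10 | *Δ* = 0.20 | *Δ* = 0.30 |
|---|---|---|---|
| 0.5 | 0.05 | 0.10 | 0.15 |
| 1.0 | 0.10 | 0.20 | 0.30 |
| 1.5 | 0.15 | 0.30 | 0.45 |

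Against 0.54 this runs from 9% (0.05/0.54) to 83% (0.45/0.54). The bottom row is hard to credit: 1.5 is about twice the pilot mean of 0.74 and 1.4 times the SD. Since 0.54 is a between-group difference, the percentages apply directly only when *Δ* is read as *Δ*₁ − *Δ*₂.

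**4. Chance variation in mix.** Group 1 has 8 × 10 = 80 baseline visits and about 8 × 7.5 = 60 at a later point. The SD of the difference in share is √(p(1 − p)(1/80 + 1/60)), which is 0.068, 0.078 and 0.085 for p = 0.2, 0.3 and 0.5. So the mix can move by 7 to 9 points (one SD) with no selection at all. This is sampling error, already part of the visit-level variance. It is not bias, though a covariate would absorb some of it.

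**5. The passages side by side.** Exploratory outcome measures collects visit type for every recorded visit as a moderation variable. Statistical analyses uses it neither in the primary model nor in its written list of moderators. Figure 2 is not available here and may show it, but an exploratory moderation analysis would still not adjust the primary estimate.

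**The case against.** Several defenses carry weight.

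- **The wait-list group.** A reader might infer that the design cannot tell training from a change in visit mix. That goes too far. Group 2 is randomized and is reassessed alongside Group 1's post-intervention assessment, and the model compares groups as well as time points, with an interaction of treatment and time. A shift from season or scheduling that affects both groups cancels. The months given for that reassessment differ (9–12 under Group 2, 12–15 under Assessing cross-contamination), but the intent is clear. What remains exposed is the within-group contrast in H1, and any shift that differs between groups.
- **No rule for choosing visits.** A reader might infer that staff pick visits by type. The article does not say so: the screening sentence describes an eligibility check. An article may leave the order of approach, consecutive or random, to the full protocol, so its absence is no finding. The exclusion wording, "Patients are excluded if they are deemed inappropriate for participation due to an acute or unstable medical condition", is close to the Table 2 item and adds little discretion.
- **Mixed visit types.** These suit a pragmatic trial and are not an error.
- **Blinded coding.** This protects the scoring, but not which visits reach the coder.
- **Restriction to visits where activity comes up.** H1 is limited to these, which removes part of the mechanism. Visit type can still affect how many of the As follow.
- **Adjusting for something training may change.** Training teaches clinicians to arrange follow-up, so visit type after training could be partly a result of it. This is a fair caution, and the reason to show the unadjusted model too. It also rules out dropping activity follow-up visits as a remedy: no such booking category is described, and those visits could be a product of the training.

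**Conclusion.** The point holds in a limited form. The plan measures visit type, treats it as potentially relevant, and then leaves it out of the primary model, while H1 rests on different patients at each time point recruited by staff who know the group. A change in mix would bias the within-group contrast. The between-group contrast is affected only by a change that differs between groups.

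The size cannot be computed from the documents. The figures in the table illustrate the mechanism and do not estimate it. A reader might take the top of that range to mean that most of the planned difference could be artifact. That would require both an implausibly large gap between visit types and a 30-point shift, and neither has support in the documents. Nor do the documents show that any shift in mix will occur. The conclusion assumes only that mean scores may differ by visit type, which the plan's own list of moderators concedes as a possibility. This is a cheap improvement to the primary analysis, not a flaw that defeats the design.

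**What to change.** Under Statistical analyses:

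1. Add scheduled visit type, as already collected from the clinic schedules, to the fixed effects of the primary mixed model.
2. Report the number and share of each visit type by group and time point.
3. Show the model without visit type as a sensitivity analysis.
4. Reconcile the moderator list in that section with Exploratory outcome measures, so that visit type appears in both or is dropped from both.

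The cost is a few lines of text and, with three categories, two model terms set against about 300 analyzable visits. No new data are needed. The one drawback is that, if training itself generates follow-up visits, adjustment could remove a little of the real effect. The unadjusted model in step 3 would show this, and the table in step 2 would let readers judge which explanation fits.

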### Recruitment of clinician participants

The principal investigator presents an overview of the study’s objectives, design, and time frame to eligible clinicians at a weekly clinician meeting. Each clinician’s full participation requires the clinician to 1) complete a 10 minute written baseline assessment, 2) attend four one-hour training sessions held during regularly scheduled provider meeting times over a four-month period, 3) consent to having 10 patient visits audio-recorded at baseline and 15 at post-intervention, and 4) complete a post-intervention survey and a 20 minute individual interview. Based on estimates from a previous pilot project, we anticipate a 10 patient visits at baseline should be sufficient; however, if the visits do not contain any discussions of physical activity, clinicians are told that the baseline assessment may consist of > 10 visits. In addition to clinicians’ informed consent, research staff explain that patient informed consent is obtained prior to any recording. For patients providing informed consent, an audio-recorder is placed unobtrusively in the exam room. Each clinician receives $60 per completed hour of the four hours of training and $5 per recorded visit. The principal investigator also explains the overall goals and procedures of the study to all clinical staff at their regularly scheduled team meetings. Staff are encouraged to forward any inquiries from patients about the study to members of the study team. The clinical practice receives a $2000 stipend for use of the facility and staff time. Clinician participants then provide written informed consent.

### Procedure for randomization

A concealed randomization procedure stratified by health center location and clinician type (physician, nurse practitioner, or physician assistant) is used to balance randomization between both groups. A series of treatment assignments in a block of five is generated by the study statistician in advance of the intervention and placed in a file accessible to the Research Assistant responsible for administering the group assignment to each clinician. Clinicians are notified of their randomization assignment by the Research Assistant immediately after providing informed consent by opening a sealed envelope with the assigned intervention category for each individual: Group 1 (Early) or Group 2 (Wait-list). Neither study clinicians nor research staff are blind to the assignment of clinicians to the early or wait-list training groups.

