### Sample size and power

The primary goal of this study is to evaluate the influence of a clinician communication intervention on use of the 5As in communication about physical activity in the post-intervention period (immediately post and at one year) compared to baseline as assessed by audio-recorded data. The sample includes a planned maximum of 15 clinicians (eight in Group 1 and seven in Group 2) measured at three (Group 1) or four (Group 2) time points. The measurements consist of a total of 25 audio-recorded patient visits from each clinician distributed across each of the evaluation points: approximately 10 recordings at baseline and seven or eight each at post- and follow-up points. Of the planned 375 recorded visits, we estimate up to 20% may be excluded from the analysis due to the patient or clinician shutting off the recorder, or equipment malfunction, thus leaving approximately 300 recorded visits (about seven per clinician per time point, or 20 total per clinician) for analysis. Pilot data with 46 recorded visits from eleven physicians showed that the average 5A score was 0.74, with a standard deviation of 1.06. Thus, with 15 clinicians and 20 patients per clinician, we will have 80% power to detect a difference of 0.54 between Groups 1 and 2, using a two-sided t-test at 0.05 significance level.

The final analyses will use a mixed effects model to incorporate correlations between the observations made by the same physician. The variance in 5A scores taken from patients within a single physician's patient panel will likely be smaller than the variance of scores taken from patients between different physicians, i.e. the intraclass correlation coefficient (the ratio of between-physician variance to the sum of between- and within-physician variances) will be larger than zero. We have conducted a series of power analyses taking this clustering into effect using a Mann–Whitney two-sample t-test of means.

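### An odd block of five within six site-by-type strata cannot ensure the balance the randomization section claims, or the planned 8/7 split of clinicians

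*Protocol article*

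**What the plan says.** All references are to the protocol article.

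- **Procedure for randomization.** A concealed procedure "stratified by health center location and clinician type (physician, nurse practitioner, or physician assistant) is used to balance randomization between both groups". On the list: "A series of treatment assignments in a block of five is generated by the study statistician". This is done before training starts. As to where the list is kept, the section says that it is "placed in a file accessible to the Research Assistant responsible for administering the group assignment to each clinician". Each clinician learns the assignment after consent, when a sealed envelope is opened. There are two groups, early and wait-list. The ratio within a block is not stated.
- **Study Setting.** "There are 15 family physicians, two nurse practitioners, and two physician assistants at the two health centers". The split by center is not given.
- **Sample size and power.** At most 15 clinicians, "eight in Group 1 and seven in Group 2". The Study design section gives 13 clinicians instead.
- **Statistical analyses.** The primary mixed model has clinician as a random effect and group, time and baseline 5A score as fixed effects. Neither health center nor clinician type is listed.

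**The concern.** Stratified blocking balances groups only if blocks are balanced when complete and strata are large enough to complete them. Here an odd block is used for two groups, so no complete block is balanced, and two centers by three clinician types make six strata for 13 to 15 clinicians. Four of those strata draw on only four people.

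With so few clinicians, chance can place most of one clinician type, or most of one center, in the same group. The listed fixed effects would not correct for this directly. A lopsided total would also depart from the 8/7 premise.

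Separately, the sentence about the file can be read as giving the person who allocates access to assignments not yet made.

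**Working it through.** **Inputs from the article:** block size 5; 2 × 3 = 6 strata; 15 physicians, 2 nurse practitioners and 2 physician assistants in the pool; planned split 8/7 of at most 15.

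**Assumptions, because the article is silent:** the split by center, and blocks that are 3:2 or 2:3 in random or alternating order.

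**1. The plan's own figure.** Because 15 = 3 × 5, one unstratified list of three alternating blocks (for example 3 + 2 + 3 = 8) gives exactly 8/7 or 7/8. With random orientation, Group 1 totals of 6, 7, 8 and 9 have weights 1:3:3:1, so 8/7 or 7/8 has probability 6/8 = 0.75. The figure is thus reproduced with certainty only on an unstratified alternating list, which is not the stratified procedure described.

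**2. Which strata complete a block.** Each nurse practitioner or physician assistant stratum holds at most 2 clinicians, so none reaches 5. If all four take part, 15 clinicians include 11 physicians and 13 include 9. However 9 or more physicians divide between two centers, one center has at least 5, so at least one block completes. With physicians 6/5 and four single-clinician strata, 10 of 15 clinicians are in complete blocks.

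**3. Total split under stratified blocks of five.** Let D be Group 1 minus Group 2.

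*Physicians 6/5, four single-clinician strata, random orientation.* D is the sum of seven independent ±1 terms: two complete blocks, one leftover physician and four singles.
- P(|D| = 1) = 2 × C(7,3)/2^7 = 70/128 = 0.547
- P(|D| ≥ 3) = 58/128 = 0.453
- P(|D| ≥ 5) = 2 × (1 + 7)/128 = 0.125

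*Physicians 7/4, four single-clinician strata, random orientation.* There are five ±1 terms, with sum S: ±1 with total probability 20/32, ±3 with 10/32, ±5 with 2/32. There are two part-blocks (of 2 and of 4), each with D = 0 (probability 0.6) or ±2 (0.2 each). Their sum is 0 (0.44), ±2 (0.48 in total) or ±4 (0.08 in total).
- P(|D| = 1) = 0.44 × 0.625 + 0.48 × 0.469 + 0.08 × 0.1875 = 0.515
- P(|D| ≥ 3) = 1 − 0.515 = 0.485
- P(|D| ≥ 5) = 0.44 × 0.0625 + 0.48 × 0.1875 + 0.08 × 0.5 = 0.158

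*Physicians 8/7, no others, alternating blocks.* The stratum of 8 has D = 0 (0.6) or ±2 (0.2 each). The stratum of 7 has ±1 (0.45 each) or ±3 (0.05 each).
- P(|D| = 1) = 0.6 × 0.9 + 0.4 × 0.5 = 0.74
- P(|D| ≥ 3) = 0.26
- P(|D| ≥ 5) = 0.4 × 0.05 = 0.02

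The other layouts tried (physicians 6/6, 7/4 and 10/1 with various non-physician strata) lie between these. For reference, a coin toss gives 2 × C(15,7)/2^15 = 0.39. If every block were 3:2 in favor of the same group, the mean split would be 9/6, and 8/7 or 7/8 would occur in only 0.27 to 0.32. With 13 clinicians, 7/6 or 6/7 occurred in 0.56 to 0.61 for the two layouts run.

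**4. All four non-physicians in one group.**
- Four single-clinician strata: 2 × (1/2)^4 = 0.125.
- Two strata of two: each pair falls wholly in a given group with probability (3/10 + 1/10)/2 = 0.2, so 2 × 0.2² = 0.08.

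**5. Block size or strata?** In the 6/5 layout five of the six strata are odd-sized. Even blocks of two then give 8/7 or 7/8 with probability 20/32 = 0.625, against 0.547 for blocks of five. Most of the shortfall in that layout comes from the number of strata.

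**6. Precision, with equal visits per clinician.** The standard error is proportional to √(1/n1 + 1/n2).
- 8/7: √(1/8 + 1/7) = 0.5175
- 9/6: √(1/9 + 1/6) = 0.5270, a ratio of 1.018
- 10/5: √(1/10 + 1/5) = 0.5477, a ratio of 1.058

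The article's detectable difference of 0.54 would become about 0.55 or 0.57.

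**The case against.** The strongest reply is that 8/7 is a planning premise attached to a maximum, not a promised result; that 15 is three blocks of five; and that a condensed article may leave list construction to the full protocol. Adjustment for baseline 5A score softens imbalance, the precision cost is small, and both groups are eventually trained. All of that is fair and limits the weight of the point. It does not remove it: the article itself fixes the block size, the strata and the purpose of balance, and these do not fit together.

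Three stronger readings are tempting, and the article does not support them.

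- *Blocks are almost never completed.* True of the non-physician strata only. The physician strata, which hold most clinicians, complete at least one block.
- *The 8/7 split cannot be reached.* It, or its mirror image, arises in more than half of allocations in the layouts tried. It is not ensured.
- *Concealment is broken.* Sealed envelopes are opened after consent, and the file may simply hold them. Access to upcoming assignments is a possible reading, not a stated fact.

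**Conclusion.** The point holds as a mismatch between the method and its stated purpose. An odd block within six strata cannot ensure balance for 13 to 15 clinicians. For 15 clinicians across the layouts tried:

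- 8/7 or 7/8 in about 52 to 74% of allocations;
- a difference of three or more in about 26 to 48%;
- a difference of five or more in about 2 to 16%;
- all four non-physicians, if enrolled, in one group in about 8 to 12%.

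These ranges rest on assumed splits by center and on random or alternating 3:2 and 2:3 blocks. They are not bounds for every possible layout. The loss of precision is minor. What matters is imbalance by site or clinician type, which the primary model addresses only indirectly, through baseline score.

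**What to change.** Preferred: the statistician allocates all consented clinicians in one step, constrained to 8/7 overall (or the equivalent for the number enrolled) and to balance on site and on physician versus non-physician. One-step allocation also removes any predictability of the next assignment. It requires that clinicians learn their group after all have consented, instead of immediately after their own consent.

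If clinicians must be assigned one by one, collapse the strata to physician versus non-physician, by site if sizes allow, with an even block. This has two limits. Small blocks are predictable. And 8/7 is guaranteed only if few strata are odd-sized: blocks of two in strata of 6, 2, 5 and 2 always give 8/7 or 7/8, but in strata of 6, 3, 5 and 1 three are odd, so the probability is 6/8 = 0.75.

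In either case, state the ratio used, reconcile it with the 8/7 plan and the number of clinicians, and say that the statistician keeps the list while the research assistant's file holds only sealed envelopes. The cost is a new list from the same statistician and a few sentences of text.
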